### 5.3 Descriptive analyses

Relevant demographic and baseline characteristics, as well as all outcomes listed in Section 2 will be summarized per trial arm for each of the analysis sets. Mean and standard deviation (or if more appropriate, median and interquartile range) will be reported for continuous variables. Frequencies and percentages will be reported for categorical variables.

In addition, outcomes will also be graphically displayed.

## 6 Interim analysis

An interim safety analysis for the Data Safety Monitoring Board (DSMB) was planned when the first 50 patients passed visit 2, and was already performed in 2016.

## 7 Safety analysis

We will descriptively analyze AEs and SAEs, including relation to the investigational medical product (IMP) up to 40 weeks PMA. We will summarize frequencies and percentages by trial arm and also show the full list of AEs with description.

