## 1 LIST OF ABBREVIATIONS AND DEFINITIONS OF TERMS

|       |                                                         |
|-------|---------------------------------------------------------|
| AE    | Adverse Event                                           |
| BW    | Birth weight                                            |
| BPD   | Bronchopulmonary dysplasia                              |
| CA    | Competent Authorities                                   |
| CEC   | Competent Ethics Committee                              |
| CRF   | Case Report Form                                        |
| eCRF  | Electronic Case Report Form                             |
| cUS   | Cerebral or cranial ultrasound                          |
| DOL   | Day of life                                             |
| DSMB  | Data Safety Monitoring Board                            |
| EDD   | Estimated date of delivery (40 weeks GA)                |
| EPO   | Erythropoietin                                          |
| FU2   | Follow up at 2 years                                    |
| FU5   | Follow up at 5 years                                    |
| GA    | Gestational age                                         |
| GCP   | Good Clinical Practice                                  |
| GMH   | Germinal Matrix Haemorrhage                             |
| ICH   | International Conference on Harmonization               |
| IMP   | Investigational Medicinal Product                       |
| ISF   | Investigator Site File                                  |
| IVH   | Intraventricular Haemorrhage, including GMH and HPI     |
| K-ABC | Kaufman Assessment Battery for Children, German version |
| MRI   | Magnet resonance imaging                                |
| NEC   | Necrotizing enterocolitis                               |
| NICU  | Neonatal intensive care unit                            |
| PI    | Principal Investigator                                  |
| PHI   | Parenchymal Haemorrhagic Infarction                     |
| PMA   | Postmenstrual age                                       |
| PVL   | Periventricular Leukomalacia                            |
| RCT   | Randomized Controlled Trial                             |
| ROP   | Retinopathy of prematurity                              |
| SAE   | Serious Adverse Event                                   |
| SD    | Standard Deviation                                      |

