## **6.6 Visit 3, postmenstrual age of 36 completed weeks gestation, 36 0/7**

At this time point the following items will be recorded, also given on SecuTrial form Visit 3. This includes items first recorded at GA 36 0/7 and a summary of treatments and complications of whole hospitalisation. If discharge home is later, some items have to be completed immediately after discharge:

- Date of visit
- Weight (g) and SD from mean weight at GA 36 0/7
- Head circumference (cm) and SD from mean length at GA 36 0/7
- Length (cm), SD from mean length at GA 36 0/7
- Hct in % and first Hb in g/dl at GA 36 0/7

cUS at GA 36 0/7, graded in normal, moderately abnormal and severely abnormal brain injury according to definitions given in visit 2

Course of haemorrhage until visit 3:

Posthaemorrhagic hydrocephalus, graded 0-3:

- 0) Restitutio ad integrum – no remaining lesions, date of last follow up
- 1) Persisting posthaemorrhagic hydrocephalus without any drainage
- 2) Persisting posthaemorrhagic hydrocephalus with repetitive but transient csf-drainage, indicate if LP, or Rickham, or both and indicate for how long
- 3) Posthaemorrhagic hydrocephalus with permanent csf-drainage, e.g. VP-Shunt

Convulsions:

- If present and/or any antiepileptic therapy, if yes specify treatment including duration
- Other abnormalities or medications related to haemorrhage
- if yes specify

Other clinical parameters until visit 3:

- Respiratory support at DOL 28 to define if mild BPD is present; indicate if FiO2 > 0.21 and/or any form of positive pressure support, CPAP or mechanical ventilation
- Respiratory support at 36 0/7 to define if moderate or severe BPD is present. BPD moderate if FiO2 > 0.21 but <0.3; BPD severe if CPAP or mechanical ventilation and/or FiO2 ≥ 0.3. These definitions are in accordance with those of the NIH adapted by the Swiss society of neonatology.
- Supplemental O2
  - Last day of supplemental O2, give date
  - Total days of supplemental O2
  - Total days of mechanical ventilation
  - Total days of CPAP
- Surfactant treatment
- Treatment with postnatal steroids, given or not given
- PDA prophylaxis, if yes indicate if indomethacin or ibuprofen
- PDA treatment, if yes indicate if indomethacin, ibuprofen, or surgical ligation
- Pneumothorax, if yes, localization
- NEC, date of onset
- FIP, date of onset
- Sepsis, date of onset, indicate if blood culture positive

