- **Apnea and oxygen desaturations** occurring in all very preterm infants due to immaturity of brain and lung and are treated with caffeine, oxygen and if severe with respiratory support.
- **Episodes of bradycardia** occur in almost all very preterm infants often in combination with apnea and oxygen desaturation.
- **Edema** occurs in almost all very preterm infants after birth due to kidney immaturity and usually disappears within few weeks. Edema may affect the whole body if severe or only typical regions, such as eyes, hands and feet.
- **Jaundice** is usually present in the first and second week of very preterm infants due to liver immaturity.
- **Skin barrier damage** is the consequence of immature skin and may occur by simply lying on the skin or touching it. Skin of very preterm infants is highly vulnerable and in regard to treatment similar to that of burn victims.
- **Gastric residuals** are often present and mainly transient in the first weeks of life.
- **Hypothermia or hyperthermia** following inappropriate incubator temperature.

2) Examples of intensive care signs not qualifying as AE:

- **Local redness of the skin** occurs always after removal of e.g. plasters, sensors, strips and is visible for few hours but sometimes for days.
- **Local trauma of the skin including local haematoma** is unavoidable when performing a heel prick, vein puncture or other medically needed invasive procedures braking skin integrity. Afterwards the damage is visible for few hours but sometimes for days.

3) Examples of AEs:

- **Anaemia** needing blood transfusion (RBC-transfusion)
- **ROP** Grade: Mild: Grade 1 → **AE**  
Moderate: > Grad 1 or plus disease → **AESI**, see below  
Severe: needing intervention → **SAE**, see below
- **BPD** Grade: Mild: no AE  
Moderate: O2 < 30% mit 36. PMA → **AE**  
Severe: O2 ≥ 30% mit 36. PMA → **AE**  
Prolongation of hospitalization due to BPD beyond EDD (requiring any respiratory support because of BPD) → **SAE**
- **Posthaemorrhagic ventricular dilatation:**  
Moderate if ventricular dilation is > 97 centile → **AE**  
Severe if ventricular dilation is > 4 mm above 97th centile. → **AE**
- **Patent ductus arteriosus:** if medical treatment is required (not preventive) and/or surgical ligation
- **Incorrect drug applications**

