### Serious adverse event

A SAE is any untoward medical occurrence that at any dose

- results in death,
- is life-threatening,
- requires subject hospitalization or prolongation of current hospitalization,
- results in persistent or significant disability/incapacity, or
- any important medical event and any event which, though not included in the above, may jeopardise the subject or may require intervention to prevent one of the outcomes listed above.

Any other medically important condition that may be not immediately life-threatening or results in death or hospitalization but may jeopardize the subject or may require intervention to prevent one of the outcomes listed above should also usually (i.e. based on medical and scientific judgment) be considered serious. For example: intensive treatment at home for allergic bronchospasm; certain laboratory abnormalities (e.g. blood dyscrasias); convulsions that do not result in hospitalisation; development of drug dependency or drug abuse.

Examples of SAEs:

- **Sepsis**, if blood culture is positive
- **NEC and/or perforation**, If Bell stage  $\geq$  IIa (pneumatosis proven) and/or perforation even without signs of NEC (e.g. Focal Intestinal Perforation, FIP)
- **ROP**, if intervention is required
- **BPD**, if severity leads to prolongation of hospitalization beyond EDD
- **Death**

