### **10.2 Recording of (Serious) Adverse Events**

The well-being of the subjects will be ascertained by medical caregiver when subjects are hospitalized and the parents when subjects are discharged. Clinical investigators and ultimately the protocol PI have the primary responsibility for AE identification, documentation, grading, and assignment of attribution to the investigational agent/intervention.

All observed or volunteered adverse drug events (serious or non-serious) and abnormal test findings, regardless of treatment group or suspected causal relationship to the investigational drug or study treatment(s) will be recorded in the patient file and subsequently in the eCRF.

Recording will be done from first study treatment DOL 5 (-2/+3 days) until discharge home. As an exception the defined AEs (ROP grade  $>1$  or Plus diseases, BPD if classified as severe at 36 PMA, and anaemia) will be recorded without time limit.

AEs or abnormal test findings felt to be associated with the study treatment(s) will be followed until the event (or its sequelae) or the abnormal test finding resolves or stabilizes at a level acceptable to the investigator.

An abnormal test finding will be classified as an AE if one or more of the following criteria are met:

- The test finding is accompanied by clinical symptoms.
- The test finding necessitates additional diagnostic evaluation(s) or medical/surgical intervention; including significant additional concomitant drug treatment or other therapy

**Note:** simply repeating a test finding, in the absence of any of the other listed criteria, does not constitute an AE.

- The test finding leads to a change in study dosing or discontinuation of subject participation in the clinical study.

All AEs, serious and non-serious, will be fully documented in the appropriate eCRF. For each AE, the investigator will provide the onset, duration, intensity, treatment required, outcome and action taken with the investigational product.

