#### More outcomes up to term equivalent age

- Mortality (binary outcome)
- White matter disease (periventricular leucomalacia, binary)
- Septicaemia (binary)

Brain abnormality scores from [Kidokoro et al. \(2013\)](#) will be used instead of the brain maturation scores described by [Leuchter et al. \(2014\)](#).

This outcome will be assessed for all recruited children in only one center, as opposed to the other cUS outcomes that were assessed in each center. An amendment of the study protocol is planned for this new secondary outcome.

These secondary outcomes are mentioned in the study protocol from Zürich, Version 1.11 from March 20, 2017, but not in the protocol paper by [[name] et al. \(2015\)](#)

- Necrotising enterocolitis or focal gastrointestinal perforation (FIP) (binary)
- Bronchopulmonary dysplasia (oxygen dependency at 36 weeks PMA, binary)
- Retinopathy (binary)
- Length of stay in hospital (days)

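### SAP 7 stops the safety analysis at 40 weeks PMA, short of the protocol's collection window, and SAP 9 does not disclose it

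*Combined protocol and SAP*

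**What the plan says.** **SAP.** Section 7 plans a descriptive analysis of AEs and SAEs, "including relation to the investigational medical product (IMP) up to 40 weeks PMA", with frequencies and percentages by arm and a complete AE listing. It does not mention adverse events of special interest (AESIs). It does not say which date places an event inside the window, or whether the listing is cut at the same point. Section 9, on deviations from the original plan, does not mention the window.

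**Protocol, collection.** Sections 6.5, 10.1 and 10.2 run AE recording from the first study treatment until discharge home. Section 10.2 exempts three events from any end date: ROP above grade 1 or Plus disease, and "BPD if classified as severe at 36 PMA, and anaemia) will be recorded without time limit".

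**Protocol, BPD as an SAE.** The AE examples in section 10.1 make this an SAE: "Prolongation of hospitalization due to BPD beyond EDD (requiring any respiratory support because of BPD"). The SAE examples repeat it: BPD qualifies "if severity leads to prolongation of hospitalization beyond EDD". Section 1 gives EDD as "Estimated date of delivery (40 weeks GA").

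**Protocol, ROP.** Section 10.1 makes moderate ROP (grade 2 or more, or Plus disease, without intervention) an AESI because concern about EPO and ROP remains. ROP needing intervention is an SAE.

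**The concern.** The analysis window is shorter than the collection window for two kinds of event: any AE or SAE after 40 weeks in an infant not yet discharged, and the named events that the protocol follows without limit. The protocol singles out ROP as the safety question for this drug, so an unexplained cut-off there is awkward.

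The cut-off also falls exactly where the BPD seriousness criterion begins. Whether that protocol-defined SAE appears in the tables then depends on a dating choice the SAP leaves open. An analyst following SAP 7 literally could report fewer serious and special-interest events than the database holds, and a reader of SAP 9 would not know.

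**Working it through.** The plan states no figure to reproduce. The check compares windows in PMA days, then tests whether the loss can be sized.

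**Window comparison**

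- SAP 7 cut-off: 40 × 7 = day 280.
- EDD (protocol 1): 40 × 7 = day 280.
- First day beyond EDD: 280 + 1 = day 281.
- BPD grading at Visit 3 (protocol 6.6, "Respiratory support at 36 0/7 to define if moderate or severe BPD is present"): 36 × 7 = day 252, which is 280 − 252 = 28 days before the cut-off.

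| Event | Protocol collects until | In SAP 7 tables? |
|---|---|---|
| Any AE or SAE dated after day 280, infant still in hospital | discharge home | No |
| ROP first reaching AESI or SAE level after day 280 | no limit | No |
| Anaemia dated after day 280 | no limit | No |
| BPD SAE, dated when it becomes serious (day 281 or later) | collected | No |
| BPD SAE, dated by BPD onset (day 252) | collected | Yes, and it can carry the SAE flag |
| AEs dated up to day 280 in infants who stay longer | collected | Yes |

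**Can the loss be sized?** Only the number of infants still in hospital at 40 weeks can be approximated, and only from another population. The earlier-trial table in protocol 4.6 gives, for its EPO arm, GA mean 29.3 weeks (SD 1.6) and hospital days mean 54.2 (SD 25.1).

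- Mean PMA at discharge: 29.3 × 7 + 54.2 = 259.3 days.
- Gap to the cut-off: 280 − 259.3 = 20.7 days.
- Every infant fixed at GA 29.3 weeks, normal distribution: z = 20.7 / 25.1 = 0.82, upper tail about 20%.
- With GA variation (SD 1.6 × 7 = 11.2 days), SD = √(25.1² + 11.2² + 2ρ × 25.1 × 11.2), where ρ is the correlation between GA and stay.
  - ρ = 0: SD = √755.5 = 27.5, z = 0.75, tail about 23%.
  - ρ = −0.9: SD = √(755.5 − 506.0) = 15.8, z = 1.31, tail about 10%.

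So roughly 10% to 23% of infants would still be in hospital at 40 weeks. This assumes normality, an assumed ρ and a trial population not selected for IVH. It counts infants present, not events. The documents give no timing of ROP or other AEs around 40 weeks, so the number of events lost cannot be derived.

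**The case against.** The strongest reply is that SAP 7 is loosely worded rather than wrong. The 40-week limit follows the clause on relation to the IMP, and the next sentence promises a complete AE listing without a stated limit. SAP 5 stages the analysis, with outcomes up to term-equivalent age first, so 40 weeks may simply mark stage one. Section 7 is descriptive, with no test or decision rule. Patient protection does not rest on it: the protocol has SAE reporting within 24 hours (10.4), monthly sponsor review of SAEs (10.4) and at least yearly DMC review (10.6).

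Much is also reported elsewhere by arm. BPD at 36 weeks and retinopathy are secondary outcomes (SAP 2.2.3), length of stay is modelled with in-hospital death as a competing risk (SAP 5.2.2), oxygen duration is summarised (SAP 2.2.4), and mortality is analysed at 2 and 5 years. The Visit 3 form records maximum ROP grade and Plus disease, and some of its items may be completed after discharge.

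This limits the consequence but does not remove the gap. SAP 7 does not tie the limit to a stage or plan an update, and SAP 9 is silent. The retinopathy outcome has no grade threshold and is headed as running up to term-equivalent age, so it does not replace an AESI summary.

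A reader might also infer that the SAP misdefines BPD. It uses "Bronchopulmonary dysplasia (oxygen dependency at 36 weeks PMA, binary"), whereas protocol 6.6 has "BPD severe if CPAP or mechanical ventilation and/or" a raised oxygen fraction, so an infant on CPAP in room air is classed differently. The documents do not support calling this an SAP error. Protocol 5.2 defines the secondary variable by oxygen dependency, and the moderate and severe grades in protocol 10.1 also use oxygen alone. The conflict lies inside the protocol, and the SAP repeats the protocol's stated secondary variable.

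**Conclusion.** The point holds as a mismatch of windows. SAP 7 is shorter than the protocol's collection period, the difference is undisclosed, and events dated after 40 weeks, late ROP at AESI or SAE level among them, fall outside the by-arm safety tables as written.

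Three stronger readings are tempting and should be resisted:

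- **That the BPD SAE can never be counted.** This is true only if events are dated by when they become serious. Under onset dating the case is in the window by 28 days. Under either rule, moderate or severe BPD at 36 weeks is still counted as an AE; what may be lost is its serious classification.
- **That all events in infants still in hospital at 40 weeks are lost.** Only events dated after 40 weeks are; those infants' earlier events stay in.
- **That about 20% measures the loss.** That figure ignores GA variation and counts infants, not events. The 10% to 23% range shows only that stays beyond 40 weeks need not be rare, under the stated assumptions.

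The size in events is unknown. The conclusion rests on reading the 40-week limit as applying to the AE and SAE analysis, which is the natural reading of the sentence.

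**What to change.** In SAP 7:

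- Analyse all AEs, SAEs and AESIs by arm from first dose to discharge home, plus ROP above grade 1 or Plus disease, severe BPD and anaemia without time limit.
- State that an AE that later becomes serious counts as an SAE even if the criterion is met after 40 weeks.
- State that the complete AE listing is not truncated.
- Add a by-arm ROP AESI summary with PMA at onset.

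If the 40-week cut is kept for the first analysis stage, record it in SAP 9 and schedule an update for later events.

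The cost is slightly more descriptive analysis; the protocol already requires the data.

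Separately, protocol 5.2, 6.6 and 10.1 should be reconciled on how BPD is defined and graded, so that the SAP outcome refers to one agreed definition. This review does not say which. Any change to the secondary outcome itself would be more than a wording edit and should be recorded as a change.

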## 8 Handling of missing data and drop-outs

We will multiply impute missing outcome and covariate data due to death or loss to follow-up in the FAS. Multiple imputation will be performed by the R package mice ([van Buuren and Groothuis-Oudshoorn, 2011](#)), and will be applied separately at each stage of analysis (see Section 5). The imputation model will use all relevant baseline variables, the randomized treatment and outcome variables collected up to the time of analysis, potentially using correlations among outcomes for imputation in case the amount of missing data differs among outcomes. We will produce  $m=20$  imputations per missing value and analyze the 20 resulting complete data sets using Rubin's rules to pool the results.

While multiple imputation assumes missingness at random (MAR), missingness not at random can be investigated using the random indicator method proposed by [Jolani \(2012\)](#), mentioned also in [van Buuren \(2018\)](#). The latter will be used for sensitivity analysis S3.

In addition, a principal stratification approach suggested by [Hayden et al. \(2005\)](#) may be applied in order to estimate the "survivor average causal effect" (SACE), as proposed for sensitivity analysis S4.

## 9 Deviations from the original statistical plan

The statistical analyses proposed in this document are generally in line with those proposed in the protocol and its published version ([name] et al., 2015), but include a few slight modifications or additions:

- Brain abnormality scores from Kidokoro et al. (2013) will be used as secondary outcomes instead of the brain maturation scores described by Leuchter et al. (2014) (see footnote above).
- Composite cUS scores will be centrally assessed, in addition to the cUS outcomes that are assessed in each center (see footnote above).
- Some outcomes were only listed in the study protocol (Zürich, Version 1.11 of March 20, 2017) but not in the published version ([name] et al., 2015) (see footnote above).
- "Other outcomes" listed in Section 2.2.4 were not listed anywhere before and are therefore only analyzed descriptively
- Due to the large number of centers compared to the number of patients we use a random intercept per center instead of modelling center as fixed effect. This allows to include additional covariates, as specified in sensitivity analysis S1.
- The sensitivity analysis S3 was added to assess the assumption of missingness at random (MAR) and S4 was added because missingness of data due to death is different from missingness that arises when a patient still alive is not measured.

These deviations and all deviations (if any) from the statistical analysis plan outlined in this document will be listed in the statistical analysis report.

